### Plans to promote participant retention and complete follow-up {18b}

Participants will be provided a minimum of one reminder email and/or phone call prior to each visit. Retention strategies include stipends upon completion of the clinical screening visit ($50) and completion of subsequent follow-up visits except the randomization visit ($190), for up to a total of $1000. In case of campus closure wherein participants will be required to travel to off-site phlebotomy clinics, additional compensation up to $200 may be provided. Finally, participants may be reimbursed for travel and/or lodging expenses if travel is required for participation.

### Data management {19}

To minimize human data entry errors, all data entered in REDCap® will be marked “unverified” for a member of the study team to later confirm the accuracy of the data entry, at which point will be changed to “complete.” Only data marked “complete” will be considered for analysis. Authorization for data exports will be limited to the study PI, clinical investigators, and biostatistician. All data will be kept for a minimum of 6 years following completion of all grant-associated activities.

### Confidentiality {27}

All data shared between institutions will follow procedures outlined in a signed data use agreement and uploaded to secure portals for confidentiality and privacy protection. All data stored in an electronic manner will be de-identified using alpha-numeric codes. Physical files which may include identifiable information will be stored in a key-locked cabinet inside a key-locked room within a keycard-locked and alarm-coded building. Only employees of the institution may be granted keycard access to the building and storage room while only clinical investigators and study coordinators will have access to the keys to the cabinets.

### Biological specimens for future use {33}

Participants will have the opportunity to consent for additional aliquots of urine and plasma to be collected and maintained for future use during the baseline visit and will be requested to provide verbal confirmation or withdrawal of consent at follow-up visits. These specimens will include up to four aliquots of 500 μL plasma and 1mL urine each for potential future exploratory analysis. Samples will be similarly de-identified and stored using the mechanisms above. No genetic analysis will be conducted.

## Statistical methods

### Statistical method outcomes {20a}

Laboratory measures will be analyzed first with descriptive statistics including mean, median, and standard deviation. Distributions will be tested for skew and transformed (e.g., natural log) as needed to reduce skew on subsequent analyses. If distributions indicate substantial non-normality that cannot be modified with transformation, non-parametric tests (e.g., Wilcoxon rank-sum) will be used.

In addition, the frequency of new, clinically significant laboratory abnormal values as outlined above will be monitored by the DSMB. The percentage of these new abnormal values per reference ranges will be reported at each time point and compared between groups by Fisher’s exact test. Assessment for changes in the distribution of each parameter will be presented as means and confidence intervals (CI) within and between groups. The significance of differences will be compared using 2-sided, unpaired *t*-tests if normally distributed and a non-parametric Wilcoxon rank-sum test of mean values between groups if non-normally distributed. Overall increases and decreases in laboratory parameters will be tested using linear mixed ANOVA with time point as a repeated factor, potentially suggestive of cumulative toxicity if trending in a clinically deleterious direction. All factors will be considered significant if *p* < .05.

Clinical activity will be measured through the CDAI. A score >150 is considered *clinically active* and is an eligibility criterion. Changes in score from baseline between groups will be compared within groups using two-sided, unpaired *t*-tests at each interval with the primary outcome as a change in value from baseline to closeout, whereas within-group changes will be compared using two-sided, paired *t*-tests. Non-parametric Wilcoxon rank-sum test of mean values between groups will be used if data are non-normally distributed.

Measures within the PROMIS-29 v.2.0 questionnaire include seven validated subscales, i.e., physical function, anxiety, depression, pain intensity, pain interference, sleep disturbance, and social interaction. Analyses will be performed by calculating descriptive statistics of mean, median, and mode of reported *T*-scores and overall PROMIS-29 questionnaire and each subscale. Welch’s *t*-test will be used to test the differences in scores between groups with *p* < .05 considered significant.

As this study will have a relatively small sample size, changes in secondary and tertiary outcome values will be considered preliminary but will be compared to results found in the phase I trial. Assessments for these outcomes, including inflammatory cytokines, gut permeability biomarkers, markers of endotoxemia, bile acids, and platelet function, will be calculated using Cohen’s *d* statistic for effect size and qualitatively compared for differences between trials using changes in values between baseline and closeout. The primary effect estimate will be for changes between baseline and closeout. This study is powered to detect a difference in Cohen’s *d* value of at least 1.2 between groups. Results will be considered evidence of a possible effect if a Cohen’s *d* value > 0.5 is observed. Statistical comparisons for significance will be considered exploratory and will be limited to unpaired *t*-tests between XN treatment groups.

The metabolite profiles and impact of XN on gut microbial composition and platelet function will be conducted with specific methods previously described by partner sites [31, 33]. Correlations between changes in CDAI and microbiota changes, inflammatory biomarker changes, and/or bile acid changes will be considered exploratory.

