### Trial design {8}

This study is a phase II, triple-blind, 1:1 drug:placebo allocation, parallel-arm, randomized, placebo-controlled trial under an investigational new drug (IND) application to the US FDA. The trial is registered with ClinicalTrials.gov (NCT04590508).

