The primary endpoint for laboratory values and vital sign measurements will be mean change from baseline to week 8, with changes also compared between groups from baseline to each additional follow-up visit (i.e., 2, 4, and 6 weeks). The frequency of new-onset or worsening laboratory values will be reported within groups throughout the trial at each biweekly visit. AEs and event severity will be reported as new-onset or worsening events spontaneously and at each biweekly visit. Together, these outcomes will provide a profile of safety and tolerability of 24mg XN for 8 weeks compared to placebo.

Secondary and exploratory outcomes include clinical disease activity, systemic inflammation (e.g., IL-10), intestinal permeability (e.g., intestinal fatty acid binding protein) and endotoxemia (e.g., LPS), platelet function, stool microbiome and bile acid composition, and the metabolic profile of XN in humans over 8 weeks. Each measurement will be collected at every biweekly clinical visit and compared between groups as mean change from baseline within groups and compared between groups at each follow-up visit. The primary endpoint for each secondary and exploratory outcome will be considered exploratory and reported as mean change within groups at week 8 from to baseline and compared between groups at each follow-up visit. The measurements to support these outcomes are outlined in Table 1.

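### The cumulative-toxicity reading rests on an overall time trend in laboratory values, with no stated comparison of that trend with placebo

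*Protocol article*

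**What the plan says.** The section Statistical method outcomes {20a} sets out a trend analysis of the laboratory safety measures: "Overall increases and decreases in laboratory parameters will be tested using linear mixed ANOVA with time point as a repeated factor". The same sentence says how a result is to be read: "potentially suggestive of cumulative toxicity if trending in a clinically deleterious direction". The next sentence sets the threshold at p < .05: "All factors will be considered significant if".

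The trial around this sentence is a "1:1 drug:placebo allocation, parallel-arm, randomized, placebo-controlled trial" (Trial design {8}). Its laboratory endpoint is compared between arms. Outcomes {12} says "The primary endpoint for laboratory values and vital sign measurements will be mean change from baseline to week 8". It also has the two arms set against each other at weeks 2, 4 and 6. The statistical section adds "Assessment for changes in the distribution of each parameter will be presented as means and confidence intervals (CI) within and between groups", tests differences with unpaired t-tests or rank-sum tests, and compares new abnormal values between groups by Fisher's exact test.

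The trend sentence differs from its neighbours. They refer to groups; it refers to overall change, names only time point, and does not say what the trend is compared with.

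**The concern.** Toxicity of XN that builds up over eight weeks would appear as a trend in the XN arm that departs from the trend in the placebo arm. In model terms that is arm-by-time. A main effect of time answers another question: whether the average over everyone moves.

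That average can move without any drug effect. Entry requires a CDAI above 150, so participants join when their disease is active, and regression to the mean or the course of disease may shift blood counts and chemistry in both arms. Rescue steroids are allowed. Outcomes {12} itself foresees non-drug change, giving new anemia linked to more diarrhea as an example. A placebo arm exists to absorb such movement, but the stated reading does not use it.

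At stake is a p-value below .05 labelled as possible cumulative toxicity when XN and placebo drifted alike, or no signal when the arms moved in opposite directions. If this test and the between-arm comparisons disagree, the article does not say which one governs the cumulative-toxicity statement.

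**Working it through.** **The plan's own figures.** The trend sentence carries no number. The nearby design figures reproduce:
- 24 / (1 − 0.25) = 32 randomized, as in Sample size {14}.
- A two-sample t-test with 12 per arm and d = 1.2, two-sided 0.05, has 80.2% power. This agrees with the detectable difference of 1.2 in {20a}.

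**Inputs.** From the protocol: 12 per arm, so N = 24; five time points (weeks 0, 2, 4, 6, 8); alpha 0.05. Assumed, because the protocol gives none: linear drift, its size, the SD and the within-person correlation.

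**Setting A: SD of baseline-to-week-8 change = 1, independent within-person errors.** The error variance per visit is 1²/2 = 0.5. With time scaled 0, 0.25, 0.5, 0.75, 1, the squared deviations from the mean sum to 2 × 0.25 + 2 × 0.0625 = 0.625.

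For a drift D shared by both arms, the noncentrality of the F-test for time is λ = N × D² × 0.625 / error variance. With D = 0.6, λ = 24 × 0.36 × 0.625 / 0.5 = 10.8.

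- Time only in the model, F(4, 92): significant in 73% of trials.
- Arm also in the model, F(4, 88): 73%.
- Arm-by-time has λ = 0, so it rejects in 5%.

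Adding arm to the model therefore does not help while the reading stays on the time main effect.

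The noncentral F values and simulation (20,000 trials) agree:

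| True drift over 8 weeks | Time, arm not in model | Time, arm in model | Arm-by-time | Week-8 change, t-test |
|---|---|---|---|---|
| Both arms +0.6 SD | 73% | 73% | 5% | 5% |
| XN +0.6, placebo −0.6 SD | 3% | 5% | 73% | 80% |
| XN only, +1.2 SD | 66% | 73% | 73% | 80% |

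**Setting B: range over correlation.** SD at each visit 1, so error variance is 1 − r. For a common drift of 0.5 SD, λ = 24 × 0.25 × 0.625 / (1 − r) = 3.75 / (1 − r).

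| Correlation r | λ | Time-only test significant | Arm-by-time |
|---|---|---|---|
| 0.5 | 7.5 | 55% | about 5% |
| 0.7 | 12.5 | 80% | about 5% |
| 0.8 | 18.75 | 94% | about 5% |

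**Dilution of an XN-only drift.** Pooling halves the slope, but the pooled slope is also more precise. With σ² the variance of one participant's slope, the pooled slope has variance σ²/24 and the between-arm difference σ²/12 + σ²/12 = σ²/6. For an XN-only slope δ, the signal-to-noise ratios are (δ/2)/√(σ²/24) = δ√6/σ and δ/√(σ²/6) = δ√6/σ, which are equal. Power is lost only because leaving arm out pushes the arm difference into the residual. In setting B:
- XN-only drift of 1 SD: 49%, 73% and 89% for time only, against 55%, 79% and 94% for arm-by-time (r = 0.5, 0.7, 0.8).
- XN-only drift of 0.5 SD: 15%, 23% and 32%, against 16%, 24% and 35%.

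The loss is about 1 to 7 points.

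**The case against.** **Arm may be in the model.** A mixed ANOVA often means a between-group factor plus a repeated factor, and the next sentence speaks of factors in the plural. A condensed article need not list every model term. This stands: a reader might infer that arm is left out, but the text does not say so. It does not rescue the stated reading, because a trend in overall values is the time main effect, and that is significant under common drift equally often with arm in the model. Overall could instead mean across the whole visit series rather than pooled over arms; the article does not settle this.

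**The wording is soft.** The result is only potentially suggestive. No stopping rule is tied to it: halting is governed by {11b}, and attribution of adverse events in {22} weighs prevalence in each group, with case-by-case review by the study team and the DSMB. This stands too. It would be wrong to infer that the plan declares toxicity from this test.

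**The arms are compared elsewhere.** A reader might infer that the safety analysis ignores placebo or would miss toxicity confined to XN. The documents do not support that. Changes are compared between arms at weeks 2, 4, 6 and 8; under common drift the week-8 t-test rejects at its nominal 5%, and for a 1.2 SD XN-only drift it has about 80% power. These comparisons limit the harm. They do not correct the trend sentence, which is the only one that refers to cumulative toxicity.

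**Conclusion.** The point holds in a limited form. The article ties a cumulative-toxicity reading to an overall time trend and states no comparison of that trend with placebo. A time main effect cannot attribute drift to XN, with or without arm in the model.

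False attribution is the main problem: about 73% of trials under a shared 0.6 SD drift, or 55 to 94% under a shared 0.5 SD drift for correlations of 0.5 to 0.8, against 5% for arm-by-time. Cancellation of opposite drifts is the second. Dilution is minor.

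The percentages depend on assumed drift, SD and error structure; the direction of the problem does not. Because the primary laboratory comparison is between arms, this is a defect in a supplementary analysis and does not undermine the primary safety comparison.

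**What to change.** Revise the sentence in {20a} to do three things:

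1. Name arm, visit and arm-by-visit as terms of the mixed model. Either keep the baseline value as one of the repeated outcomes or use it as a covariate and model only the later visits, but not both.
2. Base any cumulative-toxicity statement on the XN-minus-placebo difference in trend, with its 95% CI.
3. Report the pooled time effect as description only.

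The cost is a short text edit, with the same data, visits and software. If arm-by-time was already intended, the edit only makes that explicit. It should be made before the group codes are revealed.

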### Interim analyses {21b}

Statistical interim analyses will not be conducted; however, regular meetings of the study staff, DSMB, and auditing of the trial by third parties will be conducted as described below.

### Methods for additional analyses {20b}

Currently, no subgroup analyses are planned. If significant differences in CDAI scores are observed between groups at baseline, ANCOVA will be performed for all tests of mean differences (e.g., circulating inflammatory cytokines), adjusting for baseline CDAI scores between groups.

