## Assignment of interventions: allocation

### Sequence generation {16a}

The randomization sequence will be computer-generated and stratified according to biological sex to randomize 50% male and 50% female participants in each group.

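### Baseline adjustment depends on a significance test of baseline CDAI and then uses CDAI instead of each outcome's own baseline, which costs precision and leaves bias when the arms are imbalanced

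*Protocol article*

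**What the plan says.** All references are to the protocol article.

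- **Endpoint.** Outcomes {12}: "The primary endpoint for laboratory values and vital sign measurements will be mean change from baseline to week 8". The secondary and exploratory outcomes are likewise summarised as change from baseline.
- **Laboratory tests.** Statistical method outcomes {20a}: "The significance of differences will be compared using 2-sided, unpaired" t-tests, or a rank-sum test if the data are not normal. For laboratory parameters only, the same section adds: "Overall increases and decreases in laboratory parameters will be tested using linear mixed ANOVA with time point as a repeated factor". It names no baseline or sex covariate.
- **Other continuous outcomes.** CDAI change is compared between arms by unpaired t-tests and within arms by paired t-tests, with a rank-sum alternative. PROMIS-29 scores are compared by Welch's t-test. For secondary and tertiary biomarkers: "Statistical comparisons for significance will be considered exploratory and will be limited to unpaired" t-tests.
- **Adjustment.** Methods for additional analyses {20b} contains the only covariate adjustment: "If significant differences in CDAI scores are observed between groups at baseline, ANCOVA will be performed for all tests of mean differences". It gives circulating cytokines as an example and specifies "adjusting for baseline CDAI scores between groups".
- **Stratification.** Sequence generation {16a}: randomisation is "stratified according to biological sex to randomize 50% male and 50% female participants in each group". No stated analysis includes sex.

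The text also disagrees with itself on cytokines: {20a} limits their comparison to unpaired t-tests, while {20b} names them as candidates for ANCOVA.

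**The concern.** Three choices combine badly.

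First, whether to adjust depends on a significance test of a baseline variable. In a randomised trial any such difference is due to chance, so the test says nothing about whether adjustment would help. With 12 to 16 per arm it also misses all but very large differences.

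Second, when the rule does fire, a liver enzyme or a cytokine is adjusted for CDAI. For most outcomes the variable most likely to predict the week-8 value is the same measurement at baseline, and that is not in the model.

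Third, subtracting the baseline does not replace adjusting for it. An arm that starts high by chance tends to fall more, so a change score over-corrects whenever the baseline-to-week-8 correlation is below 1.

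At stake are the precision of the mean-change comparisons in a small trial, and the reading of effect sizes that chance baseline differences can move close to the plan's own signal threshold.

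**Working it through.** **Inputs from the protocol.** At least 12 per arm, up to 32 randomised allowing 25% attrition, and alpha 0.05 (Sample size {14}). Detectable Cohen's d of 1.2, and d above 0.5 as evidence of a possible effect, both in a paragraph that uses changes from baseline to closeout (Statistical method outcomes {20a}).

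**Assumed.** The correlation r between baseline and week 8 is not given, so a range of 0.3 to 0.9 is used. Equal variances at the two times are assumed.

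**1. The plan's own figure.** For a two-sided unpaired t-test with n = 12 per arm and d = 1.2, the noncentrality is 1.2 × √(12/2) = 2.94 on 22 df, which gives power 80.2%. Also 24/(1 − 0.25) = 32. Both figures reproduce. With 16 per arm the power is 90.7%.

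**2. What the trigger detects.** The smallest significant baseline difference, in SD units, is t(0.975, 2n − 2) × √(2/n).
- n = 12: 2.074 × 0.408 = 0.85
- n = 16: 2.042 × 0.354 = 0.72

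By construction the test fires in about 5% of randomised trials (4.7% to 5.4% in simulation).

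**3. How often imbalance arises.** The chance of a difference above 0.5 SD is 2 × [1 − Φ(0.5/√(2/n))].
- n = 12: 22%
- n = 16: 16%

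Since only about 5% trigger adjustment, roughly 22 − 5 = 17 and 16 − 5 = 11 trials in 100 would carry such a CDAI imbalance unadjusted.

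**4. Effect of imbalance in the outcome's own baseline.** A baseline difference of δ SD moves the expected difference in change by (1 − r)δ. The SD of change is √(2(1 − r)), so in SDs of change the shift is δ × √((1 − r)/2).

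| r | δ = 0.85 | δ = 0.50 |
|---|---|---|
| 0.3 | 0.50 | 0.30 |
| 0.5 | 0.42 | 0.25 |
| 0.7 | 0.33 | 0.19 |

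A difference of 0.85 SD is uncommon for any one outcome. It is the size at which a baseline test on that outcome would just become significant, but the plan applies no such test to any outcome other than CDAI.

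**5. Precision.** The variance of own-baseline ANCOVA relative to the change score is (1 − r²)/(2(1 − r)) = (1 + r)/2. Estimating the covariate slope costs 1 df and a factor 1 + 1/(2n − 4), which is 1.05 at n = 12. The noncentrality becomes 2.94/√(1.05(1 + r)/2) on 21 df. For n = 16 the same steps apply with 29 df.

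| r | Variance ratio | Power, n = 12 (unadjusted 80.2%) | Power, n = 16 (unadjusted 90.7%) |
|---|---|---|---|
| 0.3 | 0.65 | 92% | 98% |
| 0.5 | 0.75 | 88% | 96% |
| 0.7 | 0.85 | 84% | 94% |
| 0.9 | 0.95 | 80% | 91% |

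**6. The conditional rule itself.** In simulation (8,000 trials per setting), at n = 12 and r = 0.5, power was 79–80% for plain change scores, 79–81% for the plan's rule and 88% for prespecified own-baseline ANCOVA. Type I error of the plan's rule was 4.2% to 5.4% over all settings run.

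**The case against.** The strongest reply is that little is at risk. Change scores already use each outcome's baseline and remove part of an imbalance. The trial reaches its stated 80% power without adjustment. The conditional rule fires rarely and does not inflate type I error. One of the two stated power calculations concerns proportions with abnormalities or adverse events, which this issue does not touch, and the secondary outcomes are declared exploratory. All of this stands. It limits the size of the point but gives no reason to keep the baseline test.

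A reader might also infer more than the text supports:

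- **That an outcome's own baseline is never a covariate.** There is one exception: when CDAI is the outcome and the trigger fires.
- **That the trial is underpowered as planned.** At the plan's own d of 1.2 on change, it is not.
- **That omitting sex is harmful because the haemoglobin limits are sex-specific.** Those limits define a binary abnormality, compared by Fisher's exact test, so they do not enter the t-tests. Sex belongs in the model because it is the stratification factor; the loss from omitting it cannot be quantified from the document.
- **That the within-arm CDAI tests are inflated because entry requires a score above 150.** This depends on whether CDAI is measured again at baseline after screening. The text does not settle it, and the visit table is not shown.
- **That this is a detail left to the analysis plan.** The article itself fixes the trigger, the covariate and the tests.

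**Conclusion.** The point holds as a matter of efficiency and of bias conditional on imbalance. The adjustment rule recovers almost none of the available precision, responds only to very large CDAI differences, and uses the wrong covariate for every outcome except CDAI. Overall type I error is not affected.

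The size depends on the assumed correlation. The power gain at 12 per arm is about 12, 8 or 4 percentage points at r = 0.3, 0.5 or 0.7, and none at 0.9. The possible shift from a large own-baseline imbalance is a third to a half of an SD of change at r from 0.7 to 0.3. The laboratory and vital-sign mean changes, which are primary endpoints, are affected, as are the effect sizes judged against d above 0.5. This should be changed, but it does not invalidate the trial.

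**What to change.** - Delete the baseline significance test in Methods for additional analyses {20b}.
- For each continuous outcome, prespecify an ANCOVA of the week-8 value with arm, that outcome's own baseline and sex. Transform first where the distribution is skewed and keep a rank-based fallback. A mixed model over visits with the same covariates would serve equally; it is now planned for laboratory parameters only, so it would have to be extended to the other outcomes.
- If baseline CDAI is thought prognostic, name it in advance as a further covariate.
- Base conclusions on the between-arm contrast and report within-arm CDAI changes descriptively.
- Bring the sentence in {20a} that limits biomarker comparisons to unpaired t-tests into line with this.

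The cost is a wording amendment with ethics board review, made before unblinding. The analysis needs no further participants or measurements, because the baseline values and sex are already recorded. The article reports 15 of up to 32 participants completed, with those conducting the trial blinded until the primary analyses are complete, so on that status the change can still be made without knowledge of allocation.
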